## Methods

### Study design and specific aims

#### Specific aims

This ongoing study has three specific aims, which are reflected in Table 1 with associated hypotheses and primary outcome measures. First, we are implementing a multi-level system quality improvement intervention to reduce racial disparities in blood pressure control via three multi-level interventions designed to standardize the measurement of blood pressure, provide patient care management services, and offer expanded provider education resources.

**Table 1 T1:** Project ReD CHiP’s specific aims, hypotheses and main outcome measures

**Specific aims**	**Hypotheses**	**Process and outcome measures**
To perform a multi-method, staged quality improvement intervention (better blood pressure measurement, patient care management and provider education) to increase guideline concordant hypertension care and to reduce racial disparities in blood pressure control.	• Better blood pressure measurement and better blood pressure data will lead to less clinical inertia and, ultimately, better blood pressure control and less racial disparities.	• % of patients with controlled BP and % of patients with uncontrolled BP with medication titration in the last 3 months
	• Each intervention will have an additive effect and the use of all three interventions will result in a higher percentage of patients receiving guideline-concordant hypertension care and a greater reduction in racial disparities than any single combination or any combination of two interventions.	• % of patients with controlled BP and racial disparity in controlled BP
	• The care management intervention will have greater net improvement in blood pressure control at the clinic level than the provider education intervention. The provider education will have an additive and greater effect when implemented after the care management intervention than when employed without the care management intervention.	• % of patients with controlled BP and racial disparity in controlled BP
To determine the association of organizational functioning and organizational cultural competence with guideline concordant hypertension care and racial disparities in blood pressure control.	• Clinics will reflect their local surroundings and clinics with a higher percentage of minority persons will have lower organizational functioning.	• % of patients with BP control, stratified by race, compared across clinics

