#### Outcome and process measures

We are retrospectively extracting a range of process and outcome measures (already collected by the clinics) from JHCP’s EMRs (Table 5). We are collecting aggregate data at the system, clinic and provider levels. Data will be expressed as an aggregate percentage for a time period of one week, with the denominator equal to the number of patients seen in clinic by all PCPs that week and the numerator equal to the number of patients that achieved the measure as defined in Table 5. Race/ethnicity, gender, age, and presence of other chronic illnesses (diabetes, chronic kidney disease, coronary artery disease) categories will be extracted and the aggregate data will be stratified by these categories. Race/ethnicity is self-reported at the initial clinic visit.

**Table 5 T5:** Process and outcome measures used in Project ReD CHiP

**Type**	**Measure+**	**Notes and definitions**
Primary process measure	% with uncontrolled BP with medication titration in last 3 months	Uncontrolled BP ≥140/≥90 (or ≥130/≥80 if DM or chronic kidney disease); titration can be dose increase or medication change/addition
Secondary process measures	% with BP measure in EMR in last 12 months	
	% with history of pre-HTN with BP measure in last 12 months	Two clinic BPs ≥120-<140≥80-<90; not on HTN medication
	% with HTN with measure in last 6 months	Two clinic BP ≥140/≥90 OR use of a HTN medication OR ICD9 diagnosis (401.xx)
	% with HTN on a thiazide diuretic	
	% with HTN and DM on ACE-I or ARB	DM defined by ICD9 code 250.xx
	% with lipid panel performed in last 5 years^*^	May not be possible as EMR only in all clinics since March 2006
	% with BP≥135/≥85 screened for DM in last 5 years^*^	May not be possible as EMR only in all clinics since March 2006
Implementation uptake process measures	% with BP measured with OMRON	
	% of SBP and DBP measures ending in zero	
	% of eligible patients enrolled in care management	
	% completion rate for those enrolled in care management	
	Provider behavioral intention related to assessment and partnership skills	Measured at completion of the website review and at 6 months post-intervention
	Change in provider self-reported use of assessment and partnership behaviors	Measured before the website review and at 6 months post-intervention
	% of providers receiving web training at each site	Measured at 6 months post-intervention
	Provider self-reported use of HTN dashboard	Measured at 6 months post-intervention

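### The single weekly denominator conflicts with the wording of the primary process measure; taken literally, the measure mixes how many patients are uncontrolled with how often they are titrated

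*Protocol article*

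**What the plan says.** All references are to the protocol article.

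- **Outcome and process measures (text).** Data are weekly percentages, "with the denominator equal to the number of patients seen in clinic by all PCPs that week". What is counted over that base is described only by pointing to the table: "the numerator equal to the number of patients that achieved the measure as defined in Table 5". No exception is made for any measure.
- **Table 5, primary process measure.** The percentage "with uncontrolled BP with medication titration in last 3 months". The note defines uncontrolled BP and adds that "titration can be dose increase or medication change/addition". It sets no restricted denominator.
- **Table 1, first aim, first hypothesis.** The same measure is the percentage "of patients with uncontrolled BP with medication titration in the last 3 months". The hypothesis is that better measurement "will lead to less clinical inertia and, ultimately, better blood pressure control and less racial disparities".
- **Table 5, secondary process measures.** These include the percentage "with HTN on a thiazide diuretic" and a similar row for ACE-I or ARB in patients with hypertension and diabetes.
- **Stratification.** The aggregate data are to be split by race/ethnicity, among other categories.
- **Statistical analysis plan section.** The p-chart of controlled BP also uses patients seen in the week as its base. The section does not mention the titration measure.

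**The concern.** Clinical inertia is a failure to intensify treatment in patients who are uncontrolled. Its natural measure is the titration rate among those patients, and the labels in Tables 1 and 5 suggest that rate. The text gives a different base, and the person writing the extraction query cannot follow both.

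If the text is followed, a chart of the measure cannot be read as more or less inertia. The Table 1 hypothesis predicts more titration and fewer uncontrolled patients, and these two changes push the literal measure in opposite directions. In race strata, the group with more uncontrolled disease would appear to receive more active treatment even if titration were identical. That matters in a project whose purpose is to reduce a racial disparity.

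**Working it through.** **Inputs.** Table 2 gives, for sites A to F, patient numbers, percentages African American (AA) and white, hypertensive patients by race, and the percentage of these uncontrolled. As a check, the patient counts 7,755 + 4,733 + 14,887 + 3,681 + 5,628 + 6,161 sum to 42,845, the total given in the text. The article gives no titration rate, so t is an assumption, with a range of 0.20 to 0.60.

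**Formula.** Let u be the share of patients seen who are uncontrolled and t the titration rate among them. On the stated base the measure is M = u × t. On the base suggested by the labels it is t.

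**Shares from Table 2, pooled over sites.**
- AA: 3,026 uncontrolled of 15,738 patients, u = 19.2%.
- White: 2,424 of 24,095, u = 10.1%.
- Both: 5,450 of 39,833, u = 13.7%. Among the 16,976 hypertensive patients, 32.1% are uncontrolled.

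**Change over time.** M falls while t rises from t0 to t1 if u1/u0 < t0/t1, so the break-even relative fall in u is 1 − t0/t1. With u0 = 13.7%:

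| t0 → t1 (assumed) | Break-even fall in u | M before | M after, u down 10% | M after, u down 30% |
|---|---|---|---|---|
| 0.20 → 0.25 | 20.0% | 2.7% | 3.1% | 2.4% |
| 0.30 → 0.35 | 14.3% | 4.1% | 4.3% | 3.4% |
| 0.30 → 0.40 | 25.0% | 4.1% | 4.9% | 3.8% |
| 0.40 → 0.50 | 20.0% | 5.5% | 6.2% | 4.8% |
| 0.50 → 0.60 | 16.7% | 6.8% | 7.4% | 5.7% |

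With a small gain in control, M rises but understates the change. In the third row t rises by a third (0.40/0.30 = 1.33) and M by a fifth (4.93/4.10 = 1.20). With a large gain in control, M falls.

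**Race strata at equal t.** t cancels, so the AA/white ratio of M is the ratio of u: 19.2/10.1 = 1.91. In levels, M is 3.8% against 2.0% at t = 0.20, 5.8% against 3.0% at 0.30, and 11.5% against 6.0% at 0.60. By site the ratio is A 2.02, B 1.94, C 1.28, D 1.28, E 2.30 and F 2.02. Conversely, M would show no gap if AA patients were titrated 1/1.91 = 0.52 times as often as white patients.

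**Thiazide row.** On the stated base it is hypertension prevalence times prescribing. Hypertensive patients are 8,493/15,738 = 54.0% of AA and 8,483/24,095 = 35.2% of white patients, so equal prescribing reads 54.0/35.2 = 1.53 times higher for AA patients.

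**The case against.** The best defence is that the denominator sentence is a general description and was never meant for every row. It cannot apply literally to several Table 5 rows: BP readings ending in zero, enrolment among eligible patients, completion among those enrolled, providers trained, and the means. These carry their own base, and the labels of the titration measure in Tables 1 and 5 can be read that way too. This stands. It makes the defect a conflict between text and labels, and it does not show that the measure will be built wrongly. It does not remove the conflict: the titration row is a weekly patient percentage from the medical records, exactly the kind of measure the sentence describes, and nothing exempts it. Nor is this detail left to a fuller plan, since the article states a base.

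A reader might infer more than the documents support:

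- *That the measure moves against success.* It falls only beyond the break-even points above. With a small gain in control it rises.
- *That clinics or races will be ranked on it.* The stated analysis is charting over time. Table 1 attaches this measure only to the first hypothesis, and the comparison across clinics uses BP control. Stratification by race is planned; ranking is not.
- *That the thiazide and ACE-I/ARB rows become pure prevalence.* They become prevalence times prescribing.
- *That the pre-hypertension and uncontrolled rows contradict each other because an untreated diabetic patient at 132/82 can fall in both.* The rows ask different questions, and one patient may count in each.

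Table 2 describes clinic panels, not weekly attenders, and does not give the cut-off behind its uncontrolled percentages. The sizes are therefore illustrative. The direction of the race distortion needs only a higher uncontrolled share in AA patients, which Table 2 shows at all six sites.

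**Conclusion.** The concern holds as a conflict over the denominator of the primary process measure. Read literally, the text makes it u × t, which does not isolate clinical inertia. The algebra needs no assumption. The factor of about 1.9 between race strata assumes equal titration and that weekly attenders resemble the Table 2 panels. The possible fall over time depends on assumed titration rates and needs the uncontrolled share to shrink by a larger factor than titration grows. The primary outcome, controlled BP, is a separate measure and is not called into question here.

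Changing the base alone would not settle the matter. The article does not say whether a patient is classed as uncontrolled before, during or at the end of the 3-month window. If status is taken at the current visit, patients whose titration brought them under control drop out of both numerator and denominator, and the rate among those left can understate titration.

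**What to change.** Replace the single denominator in the text with a denominator column in Table 5:

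- **Primary process measure:** patients seen that week with uncontrolled BP, with uncontrolled status fixed at a stated time relative to the 3-month titration window, so that patients titrated into control stay in.
- **Thiazide:** hypertensive patients seen that week.
- **ACE-I/ARB:** patients with both hypertension and diabetes seen that week.
- **All patients seen:** keep only for measures that apply to everyone.

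Data are extracted retrospectively from existing records, so this costs a table column, one sentence and a change to the query. The price is smaller weekly denominators. With u = 13.7%, the base for the titration measure is about one seventh of patients seen. At an assumed t = 0.30, its p-chart limits are (1/u) × √[(1 − t)/(1 − ut)] = 7.31 × √(0.70/0.959) ≈ 6.2 times wider in percentage points, around a centre line 1/u ≈ 7.3 times higher. Small strata will be sparse: white patients at Site B have about 80 × 0.339 = 27 uncontrolled patients in the whole panel, so weekly race-stratified points there would carry little information.

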Primary outcome measure	% with controlled BP	Controlled BP defined as <140/<90 (or <130/<80 if DM or chronic kidney disease present)
Secondary outcome measures	% with controlled LDL	Controlled LDL defined as <130 (or <100 if DM or coronary artery disease)
	% with controlled HDL	Controlled HDL defined as >50 in women or >40 in men
	% with controlled triglycerides	Controlled triglycerides defined as <150
	% with controlled A1C	Controlled A1C defined as <7.0
	Mean SBP, DBP, LDL, HDL, triglycerides, A1C	

+Data are aggregated in one week intervals at baseline, during and after intervention roll-out for a minimum of 24 weeks.

*These measures will only be performed in clinics that have had the EMR system in place for at least 5 years.

Abbreviations: *%* percent, *BP* blood pressure, *DM* diabetes mellitus, *EMR* electronic medical record; *HTN* hypertension, *ACE-I* angiotensin converting enzyme inhibitor, *ARB* angiotensin receptor blocker, *SBP* systolic blood pressure, *DBP* diastolic blood pressure, *LDL* low density lipoprotein, *HDL* high density lipoprotein, *A1C* glycated hemoglobin.

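### The A1C outcome names no diabetic population and the stated denominator is every patient seen, so the secondary A1C and lipid control percentages partly track how many patients are tested

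*Protocol article*

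**What the plan says.** All of this stands in the protocol article under Outcome and process measures, including Table 5.

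- **Denominator.** Measures are weekly aggregate percentages, "with the denominator equal to the number of patients seen in clinic by all PCPs that week".
- **Numerator.** It is "the numerator equal to the number of patients that achieved the measure as defined in Table 5".
- **A1C.** The row reads "Controlled A1C defined as <7.0". It names no population. Mean A1C is also listed, again with no population.
- **Rows that do use diabetes.** One process measure is the percentage "with HTN and DM on ACE-I or ARB", with diabetes defined by ICD9 code 250.xx. The LDL row reads "Controlled LDL defined as <130 (or <100 if DM or coronary artery disease"), and the blood pressure rows have separate limits for diabetes or chronic kidney disease.
- **Testing as a measure in its own right.** The secondary process measures include the percentage "with BP≥135/≥85 screened for DM in last 5 years" and the percentage with a lipid panel in the same look-back.
- **Stratification.** The article also says that "presence of other chronic illnesses (diabetes, chronic kidney disease, coronary artery disease) categories will be extracted and the aggregate data will be stratified by these" groupings.

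**The concern.** Control of A1C is a question about people with diabetes. A non-diabetic patient who has the test will nearly always fall below 7.0 and so counts as controlled. A series that pools everyone can therefore improve because more non-diabetic patients were tested, while no diabetic patient's glycaemia has changed.

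The all-seen denominator adds a second problem, which the lipid percentages share. A patient with no result cannot enter the numerator but stays in the denominator, so is treated as not controlled. Each such percentage is then the share tested multiplied by the share controlled among those tested.

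The Statistical analysis plan section intends control charting of measures over time. A shift in testing after roll-out could trigger a special-cause signal on these charts and be read as better control. If testing changed differently by race, the race-stratified series would be distorted as well.

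**Working it through.** The article gives no testing rate, diabetes prevalence or expected value for these outcomes, so there is no planned figure to reproduce. The check shows which way the measure moves and illustrates by how much.

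**Inputs from the article:** the cut-off of 7.0, the all-seen denominator, and the absence of a population in the A1C row.

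**Assumptions, not in the article:**
- d, diabetic share of patients seen: 20% (range 10% to 30%)
- t_D, share of diabetic patients with a result: 85%
- c_D, share of those below 7.0: 50%
- t_N, share of non-diabetic patients with a result: raised from 10% to 30%
- c_N, share of those below 7.0: 100%

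**Formulas**
- Percentage of all seen = d·t_D·c_D + (1−d)·t_N·c_N
- Percentage of those tested = the same numerator ÷ [d·t_D + (1−d)·t_N]

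**At d = 20%**
- t_N = 10%: numerator 0.20×0.85×0.50 + 0.80×0.10 = 0.085 + 0.080 = 0.165, or 16.5% of all seen. Tested share 0.170 + 0.080 = 0.250, so 0.165/0.250 = 66.0% of those tested.
- t_N = 30%: numerator 0.085 + 0.240 = 0.325, or 32.5% of all seen. Tested share 0.170 + 0.240 = 0.410, so 0.325/0.410 = 79.3% of those tested.

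**Over the range of d, as t_N goes from 10% to 30%**

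| Diabetic share | % of all seen | % of those tested | % of tested diabetic patients |
|---|---|---|---|
| 10% | 13.25 to 31.25 | 75.7 to 88.0 | 50 to 50 |
| 20% | 16.50 to 32.50 | 66.0 to 79.3 | 50 to 50 |
| 30% | 19.75 to 33.75 | 60.8 to 72.6 | 50 to 50 |

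Both denominators move in the same direction. Only the series restricted to diabetic patients stays still.

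**Mean A1C.** Further assume means of 7.5 in tested diabetic and 5.6 in tested non-diabetic patients. At d = 20% the pooled mean goes from (0.170×7.5 + 0.080×5.6)/0.250 = 6.89 to (0.170×7.5 + 0.240×5.6)/0.410 = 6.39, a fall of 0.50 with no patient changed.

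**Within the diabetic stratum.** If the all-seen denominator still applies, the percentage is t_D·c_D = 0.85×0.50 = 42.5%. With every diabetic patient tested it would be 50%, again with no change in control.

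**Lipids.** Under the same denominator, % controlled LDL, HDL or triglycerides equals the share tested times the share controlled among those tested. It rises with lipid testing alone.

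**The case against.** The strongest reply is that the article already plans to stratify by diabetes, which gives a diabetic-only A1C series free of non-diabetic screening. This stands, and it removes much of the practical harm for A1C. It does not repair the listed overall percentage or mean A1C, which remain pooled. It also leaves the all-seen denominator in place, so untested diabetic patients still count as not controlled.

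A second reply is that the denominator sentence is a condensed, general statement, and that a fuller plan may use tested patients for laboratory measures. That would settle the lipid percentages. It would not settle A1C, because the pooled percentage among tested patients moves too (66.0% to 79.3% above).

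Third, diabetes screening need not use A1C, the article does not say that it does, and no described intervention component targets such screening. This is fair. A rise in non-diabetic A1C testing is possible but not predicted by the plan, and the sizes above are illustrations.

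Stronger readings are tempting but are not supported:
- A reader might infer that the laboratory outcomes mostly reflect samples drawn before the interventions. The article states no carry-forward rule and no testing interval. Its look-back windows belong to process measures, and its 24 weeks are a minimum: "Data are aggregated in one week intervals at baseline, during and after intervention roll-out for a minimum of 24 weeks". Which sample counts is a detail that an article may leave to a fuller plan.
- A reader might infer that the lipid outcomes rise with diabetes screening. They do not; only lipid testing would move them.

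**Conclusion.** The point holds as a badly fixed definition of secondary outcomes. Followed as written, % controlled A1C and mean A1C respond to testing of non-diabetic patients, and the A1C and lipid control percentages mix the testing rate with control. The direction for A1C is the same under either denominator, provided that non-diabetic results lie almost always below 7.0. The effect on the lipid percentages depends on taking the all-seen denominator literally.

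The size cannot be estimated from the article. Under the stated assumptions, tripling non-diabetic testing from 10% to 30% adds 16.0 points to the all-seen measure and 13.3 points to the tested-only measure at a diabetic share of 20%. Across shares of 10% to 30%, the gains are 14.0 to 18.0 and 11.8 to 12.3 points at the two ends. The importance is low: the primary outcome, % with controlled blood pressure, is untouched by this point, and the planned diabetes strata already supply part of the remedy.

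**What to change.** 1. Define % controlled A1C and mean A1C in patients with diabetes, using the ICD9 250.xx code that Table 5 already applies. Preferably fix diabetes status at baseline, so that newly found cases do not change the group over time.
2. Use patients with a result as the denominator for the A1C, LDL, HDL and triglyceride control percentages.
3. Report the testing rate beside each of these series, by race where the outcome is shown by race. A tested-only percentage still depends on who is tested, and the rate lets the reader see when that changes.

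The data come from retrospective extraction of the electronic record, so this is a change to the query and needs no new collection. The cost is smaller weekly denominators, and so wider control limits, for secondary outcomes. Fixing diabetes status at baseline also leaves out later diagnoses.

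Widening the time blocks to three months is not advised. It would reduce the 24 baseline weeks to about two points, too few for the planned rules based on eight values on one side of the mean or six in a trend.

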#### Statistical analysis plan

We will use Statistical Process Control (SPC) charting of measures over time to determine if there is a change at the system level after the implementation of the intervention and how long after implementation the change is evident [41,42]. SPC is a set of statistical methods based on the theory of variation that can be used to make sense of any process or outcome measured over time. Data will be visually inspected in a graphical display of a p-chart (for displaying proportion per time period). In this case, the x-axis will be each week of data collection (total of 24 weeks in the baseline data collection) and the y-axis will be the percent of patients seen that week with controlled blood pressure. We will distinguish normal variation from special causes (unusual changes in the pattern of data that can be assigned to a specific cause) using a range of statistically-driven tests, including: one value outside the control limits; two of three consecutive values above or below the mean and more than two standard deviations away from the mean; eight or more values falling above or below the mean; or six or more values in a row steadily increasing or decreasing (that is, showing a trend) [42].

We are also collaborating with health economists at our institution and other CPHHD centers to design and conduct a collection of cost-effectiveness analyses from health system, patient and societal perspectives, based on data from several of the ongoing interventions currently being studied by the CPHHD. We intend to capture program, patient and spillover healthcare costs, and cost offsets. The program perspective will determine the budgetary impact of implementing the interventions. Both patient and health system perspectives measure factors impacting individuals’ ability to adhere to the protocol. The success of interventions depends, in large part, on this. Additionally, interventions may have significant spillover effects, such as additional costs or cost offsets, on the healthcare system, which could impact the sustainability of the program within study sites and the likelihood of broader dissemination.

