**Methods:**

Using a pragmatic trial design, we are implementing three complementary multi-level interventions designed to improve blood pressure measurement, provide patient care management services and offer expanded provider education resources in six primary care clinics in Baltimore, Maryland. We are staggering the introduction of the interventions and will use Statistical Process Control (SPC) charting to determine if there are changes in outcomes at each clinic after implementation of each intervention. The main hypothesis is that each intervention will have an additive effect on improvements in guideline concordant care and reductions in hypertension disparities, but the combination of all three interventions will result in the greatest impact, followed by blood pressure measurement with care management support, blood pressure measurement with provider education, and blood pressure measurement only. This study also examines how organizational functioning and cultural competence affect the success of the interventions.

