#### Trial status

The blood pressure intervention was introduced to all six clinic sites by September 2011 (Figure 3). In three of the clinics, the care management intervention starts six to nine months before the provider education intervention and in the other three clinics the care management intervention starts six to nine months after the provider education intervention. At the time of this writing, care managers have been embedded in one clinic site and are beginning to expand their services to two other sites. Providers at two of the sites have access to the dashboard and have seen the online communication training videos. We will continue to stagger the introduction of the care management and provider education interventions to the remaining clinics over the next two years.

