Limitations of the study deserve mention. First, it is not mandatory for physicians to view the communications skills training sessions or utilize the elements on the dashboard. This may result in reduced uptake and a potential dilution of the overall effect of the provider education intervention. Additionally, the care management intervention may not be intensive enough to encourage sustained behavior change if patients do not attend all three sessions. Furthermore, in the blood pressure measurement intervention, we are making every attempt to collect high quality data, but are primarily relying on self-reports and qualitative measures to assess adherence to the blood pressure measurement protocol. This will limit the precision with which we can examine adherence. The main limitation for the organizational assessments is that some of our measures will only be collected once, so we will not know how these have changed over the course of the intervention. However, other organizational measures will be collected multiple times, for both intervention and non-intervention sites, allowing estimation of change over time and relative to an unexposed group. Lastly, in a complex healthcare delivery system, additional system-wide or practice-based quality improvement efforts may confound the results, for example, efforts to meet the ‘meaningful use of EMRs’ metrics may improve health system-patient communication. Because data will be evaluated on the system level, other unanticipated factors, in addition to unique clinic level issues, could limit the study’s ability to detect changes in our desired outcomes.

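### The analysis section evaluates change at system level, against the abstract's clinic-level promise and a roll-out that starts two of the three interventions clinic by clinic

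*Protocol article*

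**What the plan says.** The article describes the level of analysis in five places.

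- **Statistical analysis plan:** control charts are used to "determine if there is a change at the system level after the implementation of the intervention", and to see how long after implementation the change appears.
- **Discussion, limitations paragraph:** "Because data will be evaluated on the system level, other unanticipated factors", together with local clinic issues, might limit the ability to detect change.
- **Abstract, Methods:** the interventions are staggered and the charts are used "to determine if there are changes in outcomes at each clinic after implementation of each intervention".
- **Table 1, first aim:** "The care management intervention will have greater net improvement in blood pressure control at the clinic level than the provider education intervention". The same aim states that effects add up, and that provider education works better after care management than without it.
- **Outcome and process measures:** "We are collecting aggregate data at the system, clinic and provider levels".

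The Trial status section gives the roll-out. "In three of the clinics, the care management intervention starts six to nine months before the provider education intervention", and the other three clinics take the reverse order. "We will continue to stagger the introduction of the care management and provider education interventions to the remaining clinics over the next two years". For blood pressure measurement the text says only that all six sites had it by September 2011.

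**The concern.** The first two places and the next two describe different main analyses. The difference matters because the staggered, opposite-order roll-out is what allows the effects of care management and provider education to be separated.

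In most weeks of the roll-out, a pooled series mixes clinics with neither intervention, with one, with the other, or with both. For these two interventions it has no single point after which implementation has happened, so the time from implementation to change is undefined too. The additive, comparative and order hypotheses in Table 1 cannot be read from it.

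Reducing racial disparity is a central aim, and race is closely tied to clinic in Table 2. The system racial gap can therefore move during roll-out simply because of which clinic starts first.

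**Working it through.** **Inputs.** Table 2 gives, by site and race, the number of patients with hypertension and the percentage uncontrolled. The column totals reproduce the article's own figures of 42,845 patients and 45 primary care providers. Hypertensive patients total 8,493 African American (AA) and 8,483 white, 16,976 in all.

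**System gap in percentage uncontrolled.**
- AA: (2,940×33.1 + 2,777×38.8 + 1,493×29.7 + 359×40.1 + 331×40.5 + 593×42.8) / 8,493 = 35.63%.
- White: (705×29.2 + 80×33.9 + 4,209×24.3 + 1,362×34.9 + 650×37.1 + 1,477×30.6) / 8,483 = 28.58%.
- Crude gap: 7.05 points.

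**Within and between clinics.** The clinic gaps for A to F are 3.9, 4.9, 5.4, 5.2, 3.4 and 12.2. With Mantel-Haenszel weights, AA×white/(AA+white), the pooled within-clinic gap is 5.96. With AA weights it is 5.11. If AA patients had the white rate of their own clinic everywhere, the system would still show 1.94 points; 5.11 + 1.94 = 7.05.

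**A 10-point gain, equal in both races, at one clinic only.** The system percentage moves by 10 × the site's share of hypertensive patients. The system gap moves by 10 × (site's share of white hypertensives − site's share of AA hypertensives).

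| Site | Share of all | System % moves by | White share | AA share | Gap moves by | System gap becomes |
|---|---|---|---|---|---|---|
| A | 21.5% | 2.15 | 8.3% | 34.6% | −2.63 | 4.42 |
| B | 16.8% | 1.68 | 0.9% | 32.7% | −3.18 | 3.87 |
| C | 33.6% | 3.36 | 49.6% | 17.6% | +3.20 | 10.25 |
| D | 10.1% | 1.01 | 16.1% | 4.2% | +1.18 | 8.23 |
| E | 5.8% | 0.58 | 7.7% | 3.9% | +0.38 | 7.43 |
| F | 12.2% | 1.22 | 17.4% | 7.0% | +1.04 | 8.09 |

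No clinic's own gap changes in any row. Each set of shares sums to 100%, so the gap changes sum to zero over the six clinics. If shares followed all patients rather than hypertensives, they would run from 3,681/42,845 = 8.6% (D) to 14,887/42,845 = 34.7% (C), with the same implication.

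**Would the chart signal?** The article gives no weekly counts, so visit rates are assumed. At 2 or 4 visits per hypertensive patient per year, the system sees 16,976×2/52 = 653 or 16,976×4/52 = 1,306 a week. The weekly standard error is √(0.679×0.321/n) = 1.8 or 1.3 points. A simulation applied all four signal rules of the analysis section, with 3-SD limits, 24 baseline and 24 later weeks, no overdispersion and 3,000 runs. The ranges below run from 2 to 4 visits a year.

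| 10-point gain at | System chart signals | That clinic's own chart signals |
|---|---|---|
| A | 95–100% | 100% |
| B | 83–98% | 100% |
| C | 100% | 100% |
| D | 55–75% | 100% |
| E | 34–45% | 97–100% |
| F | 65–86% | 100% |

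With no change at all, the system chart signals in about 24% of runs.

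**The case against.** The strongest reply is that a clinic-level analysis is stated: the abstract promises it, Table 1 relies on it and clinic aggregates are collected. An article condenses a fuller plan, which may specify clinic charts. This stands against inferring that the study has settled on a system-only analysis and discards the staggering. It does not remove the conflict: the section that sets out the analysis names the system level, and the limitations paragraph reasons from that.

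A reader might also infer that one clinic's effect would be invisible on the system chart. The documents do not support that. The run rules would usually catch a 10-point gain at A or C. The effect is diluted and cannot be attributed, and it is nearly lost only at the smallest site.

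Nor should the gap be said to drift with ordinary clinic mix. A 25% change in one clinic's volume moves it by only 0.04 to 0.33 points. The ±3.2-point shift is a roll-out artefact with one clinic live. Table 3 brings all six clinics into every intervention, and an equal gain in all six leaves the system gap unchanged.

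Finally, the crude and stratified gaps measure different things. The between-clinic 1.94 points is real disparity in a project whose conceptual model includes organizational and community factors. The system gap should not be dismissed as an error or reduced to mere description.

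The absence of a common start date is clear for care management and provider education. For blood pressure measurement the text is not specific, and the timeline figure is not available here.

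**Conclusion.** The concern holds in this form. The article contradicts itself on the level of analysis, and the system-level wording does not fit the clinic-by-clinic, opposite-order starts of care management and provider education. Followed as written, it would dilute a one-clinic effect to 6–34% of its size, leave any signal without a clinic or intervention to credit, and leave the additive and order hypotheses untestable. While clinics are unevenly exposed, it could also show the racial gap narrowing or widening by up to 3.2 points on 7.05 when both races benefit equally.

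The contradiction and the gap decomposition rest on the text and Table 2 alone. The dilution and gap shifts also need the illustrative 10-point gain, and they scale with it. They count only AA and white hypertensive patients and assume visits in proportion to patient numbers. The signal rates depend further on the assumed visit rates and on no overdispersion.

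**What to change.** In the statistical analysis section and the limitations paragraph, make the main analysis one p-chart per clinic, aligned to that clinic's own start date for each intervention. This brings both places into line with the abstract and Table 1. Keep the system chart as a supplement.

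For disparity, report a clinic-stratified racial gap, for example with Mantel-Haenszel weights, beside the system gap. State that the system gap is a separate, valid measure that includes the between-clinic part, and that it should not be read as an intervention effect on disparity while clinics are unevenly exposed.

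The cost is small, because the clinic-level data stratified by race are already being extracted. It means rewording and somewhat more analysis. The race-specific series cannot stay weekly where one race is sparse: Site B has 80 white hypertensives, about 80×4/52 = 6 a week at 4 visits a year and 3 at 2 visits. Those series need longer intervals or pooling. Six charts also give more chances of a false signal than one, so each signal should be read against that clinic's own start dates.
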